## Background

Physical activity (PA)—understood as any body movement that requires energy expenditure above the resting metabolic rate—is a key behaviour for people living with type 2 diabetes mellitus (T2DM) [1, 2]. In these patients, increasing daily PA has a dose-response relationship with markers of glucose control (i.e., HbA1c) [3]. Moreover, being physically active also produces psychological and social benefits: it improves patients’ quality of life and reduces the healthcare costs associated with physical inactivity [4–6].

PA recommendations in patients with T2DM include at least 150–300 min of moderate-to-vigorous intensity (MVPA) most days of the week with a multicomponent training including aerobic and muscle-strengthening activities [7]. In addition, the amount of time spent being sedentary should be limited [8]. In this regard, adhering to regular PA—understood as not dropping out of the newly adopted PA behaviour [9]—is a way to control T2DM and promote self-management [10–12]. To achieve these goals, the preferred modality of health care professionals (HCP) to encourage and increase PA is walking. Walking 30 min a day is a popular recommendation for increasing PA and reducing time spent being sedentary that HCPs are able to make in health care consultations with these patients [13]. However, after decades of primary care-based PA recommendations and interventions, patients report dropout rates of 20–50% within the first 3–6 months of intervention [14, 15], and in the long run (e.g. 12–24 months), the interventions seem ineffective [16, 17].

To deal with this dropout problem, high-intensity interval training, which requires less time to achieve the same benefits as moderate intensity [18], has been proposed as a possible solution to overcome one of the most frequently reported barriers to adherence (namely, lack of time) [19, 20]. However, the advanced skills required and the necessary good physical condition to withstand these kind of protocols [21, 22] may not be a suitable solution for most patients [23]. Another option to reduce patients’ PA drop out is Nordic walking (NW) [24]. NW provides more health benefits (e.g. glucose control, cardio-respiratory fitness, flexibility and upper-body strength) than merely walking [25, 26], and it is easier to perform than high-intensity interval training [27]. However, although NW seems to be more enjoyable than simply walking, the PA drop-out ratio remains high [24].

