### Sample size

We calculated the sample size (*n* = 144) in relation to the drop-out ratio in PA interventions showed by other studies (15%) [45] with a balanced one-way analysis of variance power calculation of 80%, a significance level of 5%, an expected drop-out rate in participants of 15% and an effect size of 0.5. As a result, 48 participants will be needed in each group in the three-arm randomized controlled trial.

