## Discussion

This study proposes a comprehensive approach, taking into consideration multiple levels of influence on PA adherence, to find out solutions for HCPs to prescribe PA efficiently in patients living with T2DM. First, we want to evaluate the effectiveness of a theory-driven PA intervention based on SENWI in people living with T2DM that will be implemented in real-life Spanish primary care clinical practice. Second, we wish to explore the feasibility on the PA adherence process in T2DM patients while participating in the SENWI programme, and to understand the HCPs’ opinion regarding its applicability in the Spanish healthcare system. As a result, the applicability of this study will be the preparation of easy and friendly guidelines for HCPs to apply SENWI during consultations.

PA interventions for patients with T2DM have been focused on the type of training (e.g. walking) [24] or intensity (e.g. high-intensity PA) [23, 63]. Despite their effectiveness in adopting a new behaviour, PA adherence has not yet been addressed. As these interventions ignore the social complexity of PA, poor results have been gathered in the last decade of research to be used in day-to-day life in patients with T2DM [64, 65]. More than 40% of patients do not adhere in the long run to HCP recommendations on lifestyle changes when they include PA [28]. As a result, although PA is a key behaviour for patients with T2DM to manage their illness, HCPs feel powerless to prescribe PA efficiently to improve adherence and avoid dropout [42].

Our hypothesis is that the SENWI approach may be useful to HCPs to deal more efficiently with PA adherence in patients with T2DM in social complex situations. For example, instead of just motivating or informing patients about the importance of PA, HCPs should recommend how to avoid barriers related to PA (e.g. helping to re-schedule sessions in case some problem arises or proposing other PA activities to do in their daily lives), where to do it (e.g. open green areas or parks) and with whom (e.g. group activities). Therefore, we propose that HCPs should consider the different levels of influence that could affect T2DM patients’ PA adherence. To do that, other studies have proposed a three-step ‘action management’ approach: prepare the user, structure the action and design the context [66].

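### The sample size uses 15% both as the activity drop-out ratio and as participant loss, below the Background's own 20 to 50%, and 48 per arm at 80% power does not follow from the stated inputs

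*Protocol article*

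**What the plan says.** The Sample size section opens: "We calculated the sample size (*n* = 144) in relation to the drop-out ratio in PA interventions showed by other studies (15" per cent, with a citation. The calculation is described as made "with a balanced one-way analysis of variance power calculation of 80" per cent, with "a significance level of 5" per cent, "an expected drop-out rate in participants of 15" per cent and "an effect size of 0.5". It concludes that "48 participants will be needed in each group in the three-arm randomized controlled trial".

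The Background, writing of primary-care PA recommendations and interventions, says that "patients report dropout rates of 20–50% within the first 3–6 months of intervention". The Discussion adds: "More than 40% of patients do not adhere in the long run to HCP recommendations", where the advice concerns lifestyle change that includes PA.

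Three other parts of the article bear on the point:

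- **Outcome definition.** Table 4 and the section on the PA drop-out ratio make stopping PA a primary outcome. It is judged by attendance below a threshold during the programme and by self-report afterwards.
- **Time points.** Assessments fall at baseline and at months 3, 12 and 24.
- **Analysis.** The Data analysis section specifies intention to treat on the data obtained, with no replacement of missing values.

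**The concern.** Two different quantities carry the same number. One is the proportion of participants who stop being active, which this trial sets out to measure and reduce. The other is the proportion who cannot be measured, which is what a sample size is inflated for. The section describes 15% as the first and uses 15% as the second, and it attaches no time point to either.

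Read as the first quantity, 15% lies below the bottom of the range in the Background, and that range covers only the first 3 to 6 months of a trial that follows participants to month 24. The reader is not told why a lower figure was chosen.

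Read as the second quantity, it matters because the analysis uses observed data only, so participants who are not measured reduce the precision of each comparison. The activPAL outcome also needs at least four valid days of recording.

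The stated 80% power depends on this input and on an effect size whose metric is not given. If the paragraph cannot be reproduced, nobody can tell how much loss the trial tolerates.

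**Working it through.** **Inputs, all from the Sample size section:** three equal arms, one-way analysis of variance, alpha 0.05, power 80%, effect size 0.5, loss 15%, 48 per arm (144 in total).

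**Method.** For n evaluable per arm, power is the probability that a noncentral F variable with 2 and 3(n − 1) degrees of freedom and noncentrality 3nf² exceeds the central 5% critical value. Inflation for loss L is n / (1 − L), rounded up.

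**Step 1. Readings of the effect size.** The metric is not stated, so each plausible reading was tried.

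- Cohen's f: f = 0.5.
- Standardised difference d = 0.5 between the extreme arms, third arm midway: f = 0.5 × √(1/6) = 0.204.
- The same, with two arms equal: f = 0.5 × √8 / 6 = 0.236.
- The two-group conversion f = d/2 = 0.25.

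**Step 2. Attempt to reproduce 48 per arm.**

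| Reading | Evaluable n per arm for 80% | After 15% inflation | Total |
|---|---|---|---|
| f = 0.5 | 14 | 14/0.85 = 16.5, so 17 | 51 |
| f = 0.25 | 53 | 53/0.85 = 62.4, so 63 | 189 |
| f = 0.236 | 59 | 59/0.85 = 69.4, so 70 | 210 |
| f = 0.204 | 79 | 79/0.85 = 92.9, so 93 | 279 |

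A two-sample comparison with d = 0.5 needs 63 per arm, or 75 after inflation (63/0.85 = 74.1). A one-sided version needs 50, or 59 after inflation. At alpha 0.10 some readings come close: f = 0.25 gives 42, inflated to 50, and f = 0.236 gives 48 before any inflation. The section states 5%, however. No reading tried reproduces 48 per arm from the stated inputs.

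**Step 3. Power that 48 randomised per arm provides.** Evaluable n = 48 × (1 − L).

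| Loss | n per arm | f = 0.5 | f = 0.25 | f = 0.236 | f = 0.204 |
|---|---|---|---|---|---|
| 0% | 48.0 | >99.9% | 76.1% | 70.8% | 57.4% |
| 15% | 40.8 | 99.9% | 68.5% | 63.0% | 50.1% |
| 20% | 38.4 | 99.9% | 65.6% | 60.1% | 47.6% |
| 30% | 33.6 | 99.6% | 59.2% | 53.9% | 42.2% |
| 40% | 28.8 | 98.8% | 52.1% | 47.2% | 36.6% |
| 50% | 24.0 | 96.9% | 44.3% | 40.0% | 30.9% |

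With f = 0.5, 80% power needs 13.9 evaluable per arm, so it is lost only when loss exceeds 1 − 13.9/48, or about 71%. With d = 0.5, power is below 80% even with no loss at all.

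**Step 4. The drop-out figures side by side.**

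| Section | Figure | What it describes | Horizon |
|---|---|---|---|
| Sample size, first use | 15% | Drop-out ratio in PA interventions, cited | Not stated |
| Sample size, second use | 15% | Expected loss of participants | Not stated |
| Background | 20 to 50% | Dropout from primary-care PA recommendations and interventions | 3 to 6 months |
| Discussion | Over 40% | Not following lifestyle advice | Long run |

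The first and third rows describe the same kind of quantity and disagree. The second row is the only figure in the document for loss of participants. The fourth is neither a retention rate nor a programme drop-out rate.

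**The case against.** The strongest reply is that stopping PA is not the same as being lost. Under intention to treat, a participant who stops walking can still be weighed, answer the monthly question about activity and have HbA1c read from the health-system dataset. For the drop-out outcome that person is an event, not a missing value. On this view the 20 to 50% and the 15% can both be right. The 15% also has a citation, and the studies behind it may differ from those behind the Background's range. None of those sources can be seen here.

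Much of this stands. It means that neither the Background's range nor the Discussion's figure disproves a 15% allowance for loss to measurement. It does not clear the paragraph, because the section itself calls its 15% a PA-intervention drop-out ratio and never draws the distinction the reply relies on. A citation shows where the figure came from, not why it lies below the range quoted elsewhere.

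Three stronger readings are tempting, and the documents do not support them.

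- **Power falls from 80% as loss rises above 15%.** A reader might assume that 48 per arm with 15% loss gives exactly 80%, solve for f = 0.284, and find power of 77%, 64% and 55% at 20%, 40% and 50% loss. That effect size is not in the protocol, and the step takes the stated 80% as true when it cannot be reproduced.
- **The Discussion shows that over 40% will be lost.** A reader might infer this, but the figure concerns adherence to advice.
- **Power on the drop-out outcome itself is low.** That needs a comparison rate between arms, and the protocol gives none.

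**Conclusion.** The point holds in a limited form. One figure of 15% serves for two different quantities. As a PA drop-out ratio it sits below the Background's 20 to 50%, with no explanation. The stated 80% power for 48 per arm is not what the stated inputs give: at 15% loss it is about 99.9% if 0.5 is Cohen's f and about 50 to 69% if it is a standardised difference. At 50% loss the corresponding figures are about 97% and 31 to 44%.

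On each reading tried, moving loss between 15% and 50% leaves power on the same side of 80%. Retention alone therefore does not decide whether the target is met; the undefined effect size matters more.

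These results assume the one-way comparison and 5% level that the section states, equal arms and equal loss in each arm. They say nothing about whether 144 is too few or too many, since that depends on which effect size was meant. This is a planning input that should be corrected; it does not show that the trial is unsound.

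**What to change.** Rewrite the Sample size paragraph so that it does four things:

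1. Names the effect-size metric and, if it is a standardised difference, the pattern of arm means and the outcome and time point to which it applies.
2. Gives the expected loss to measurement as its own assumption, with the time point it refers to (month 3, 12 or 24).
3. Gives the expected PA drop-out ratio separately, as an assumption about an outcome, and explains how it fits with the 20 to 50% in the Background.
4. States the power that 144 participants provide over 15 to 50% loss, using the chosen metric, in place of the present 80%.

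The cost is one paragraph and a short table. Enrolment, visits and interventions do not change. The stated power will change: upwards if Cohen's f was meant, downwards if a standardised difference was meant.

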### Qualitative study sample size

A subsample for the qualitative study will be selected from those participants that will be enrolled in the intervention groups using a convenience sampling. Physiotherapists that are not part of the usual clinical team and that will deliver and prescribe PA during the intervention and HCPs already in contact with T2DM participants will also be engaged in the qualitative study. The collection of the sample will finish when saturation is achieved.

According to COREQ guidelines, and prior to formal data capture, the discussion-focus group process will be trialed three times to test and validate the discussion guide [46]. We will introduce open questions regarding participants’ beliefs to enrich the interview guide. In a spirit of continuous improvement, the guide will be reformulated and improved throughout the study after each meeting. Discussions will be terminated when the facilitator/interviewer feels that the research team could not develop more key themes.

Informed consent will be given voluntarily, and confidentiality of personal information followed the Protection of Personal Data and the guarantee of digital rights and the General Regulation (EU) 2016/679, of 27 April 2016, on data protection and complementary regulations. The Declaration of Helsinki statement of ethical principles for medical research involving human subjects will be followed [47].

### Patient public involvement

Patients had an involvement active role in the development of the protocol through a qualitative study carried out previously by the research team [34].

### Randomization and blinding

A computerized random-number generator (http:// www.randomization.com, created by [name], Tufts University) will be used to randomize eligible participants at the level of the individual participant, stratified by sex and age, in blocks of ten.

Concealed randomization will be conducted by the research member after each participant has been included in the study, has been assigned an identification code and has completed the study baseline assessment. Nurses from CAPs/Hospitals will enrol the participants.

Allocation concealment will be ensured as the random-number generator will not be released until the patient has been recruited into the trial, which takes place after all baseline measurements have been completed. Participants will be notified personally face-to-face.

The design is open label with only outcome assessors being blinded so unblinding will not occur. The researchers carrying out the baseline assessments will be blind to group allocation. The statistician will also be blind to group allocation until the completion of the statistical analysis. Participants will be asked not to reveal group allocation when undergoing follow-up measurements. To assess the extent to which blinding has been preserved, researchers will record the number of cases in which allocation was revealed.

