### Participants

A total of 144 participants (randomized in two intervention groups and one control group) will be included in this study. The study will be conducted in the Central Catalonia health area (Spain). Participants will be recruited from Monistrol de Montserrat *Primary Care Center* (CAP), Vic Sud CAP (Vic), CAP les Bases (Manresa), Hospital *Sant Bernabé* (Berga) and Anoia CAP (Igualada).

Inclusion criteria for eligibility will include participants (i) with T2DM, (ii) that have no major physical limitations prescribed by the doctor or any HCP and (iii) that are physically inactive according to the Spanish version of a Brief Physical Activity Assessment Tool – SBPAAT screening tool [44]. Participants will be excluded if they (i) are pregnant or have T2DM due to gestation; (ii) are unable to freely consent to take part in the study; (iii) are unable to understand the study materials or PA intervention; (iv) have complications such as neuropathy, retinopathy and nephropathy; (v) have relative or absolute contraindications to do PA; and (vi) have a body mass index over 34.9 kg/m^2^ since Nordic walking uses poles that require free arm mobility that is impaired by a body mass index over 35 kg/m^2^.

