### Comparator group 1: NW programme

Before the intervention, participants will do a beginner’s class in NW over 2 days with an instructor. This will be done at the same place where the intervention will be conducted (i.e. outdoors near the CAPs). After these two sessions, the 12-week intervention with two sessions/week will start. Sessions will be progressive: the first month will last for 30 min, the second month 35 min and the third month 40 min (plus 10-min warm-up and 10-min cool-down in each session). Track paths will be flat and will not have more than 100-m cumulative altitude. The meeting point will be at the CAP facilities.

Participants will be scheduled at two different times (e.g. midday and afternoon). Each group will receive 26 NW sessions. Patients will receive a schedule with all 12-week sessions.

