## Trial status

The call for participants in Monistrol de Montserrat CAP began on 1 February 2022. We had enrolled 40 volunteers at the time of submission of the manuscript. Recruitment is expected to start at Hospital Sant Bernabé in September 2022, at Vic Sud CAP in November 2022, at Anoia CAP in January 2023 and at CAP les Bases in February 2023, at Anoia CAP. Data analysis will be completed by December 2023. Trial status: Recruiting participants.

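### Randomisation leaves out centre and uses blocks of ten for three arms, so arms can be uneven within centres that differ in place and season

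*Protocol article*

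**What the plan says.** Under Randomization and blinding, the protocol article will "randomize eligible participants at the level of the individual participant, stratified by sex and age", with a block size of ten. No other section names centre as a stratification factor. The Sample size section states that "48 participants will be needed in each group in the three-arm randomized controlled trial", so the intended ratio is 1:1:1 with 144 people in total.

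The Participants section lists five recruiting sites. Study interventions and the Nordic walking (NW) programme section place the NW and SENWI sessions outdoors in green areas near each site, with the site as meeting point. The NW section adds: "Participants will be scheduled at two different times (e.g. midday and afternoon)".

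The Trial status section starts the first site in February 2022 and the second in September 2022. The rest follow "at Vic Sud CAP in November 2022, at Anoia CAP in January 2023 and at CAP les Bases in February 2023". Forty people were enrolled when the manuscript was submitted.

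The Data analysis section names treatment group and time as factors, and lists age, gender and social characteristics as covariables. Centre is in neither list.

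**The concern.** Centre determines where people walk. Because of the staggered opening, it also largely determines the time of year of the 12 outdoor weeks and of the post-intervention activity recording. The primary outcomes include session attendance and measured activity, and both could plausibly vary with place and weather. The allocation rule controls sex and age but leaves the split of arms within a centre to chance. The block size adds to this, because a block of ten cannot hold equal numbers from three arms.

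Two things are at stake. One is chance imbalance of arms across site and season, in analyses that, as described, have no centre term. The other is practical: NW and SENWI are delivered to groups at a centre, and SENWI relies on group discussion, so arm numbers per centre affect delivery.

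**Working it through.** **Inputs from the article.** 144 people, three arms, five centres, block size ten, strata sex and age. Average centre size is 144 / 5 = 28.8, and average arm size within a centre is 28.8 / 3 = 9.6.

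**Assumptions, because the article does not give these figures.**
- Centre sizes are 29, 29, 29, 29 and 28.
- There are four equally likely sex-by-age strata (two age bands).
- A block of ten holds 3 + 3 + 3 = 9 places plus one extra place given to a randomly chosen arm.
- Recruitment is strictly sequential, partly overlapping (the last three centres together) or fully concurrent.

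**Method.** About 3,000 trials were simulated for each case. Each person takes the next place in the block list for their stratum, shared across centres as the stated strata imply. For each centre, gap = largest arm minus smallest arm. With 29 people, a split of 12/9/8 has a gap of 4, and 13/9/7 has a gap of 6. Repeated runs agreed to within two to three percentage points.

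**Results under the stated rule.**

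| | Sequential | Partly overlapping | Concurrent |
|---|---|---|---|
| Mean gap per centre | 3.7 | 4.1 | 4.8 |
| Centres with gap of 6 or more | about 18% | about 25% | about 35% |
| Trials with at least one such centre | about 60% | about 75% | about 86% |

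The last two rows agree roughly, treating centres as independent: 1 − 0.82^5 = 0.63 and 1 − 0.65^5 = 0.88.

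**Small arms.** Some centre-by-arm cell holds 5 or fewer people in 14% (sequential) to 40% (concurrent) of trials. For the SENWI arm alone, this is 5% to 16%.

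**Sensitivity.**
- With six strata, at least one centre has a gap of 6 or more in 73% (sequential) to 87% (concurrent) of trials.
- Over other centre sizes (40 in the first centre and 26 in each other, or 64 and 20), the range is 50–87%.
- With 40 and 26, an arm of 5 or fewer occurs in 34–61% of trials, and in the SENWI arm in 13–27%.

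**Precision.** For two arms A and B compared with adjustment for centre, information is proportional to the sum over centres of nA·nB / (nA + nB). With perfect balance this is 48 × 48 / 96 = 24. Under the stated rule the average shortfall is about 3% (sequential) to 5% (concurrent).

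**Alternatives.**

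| Rule (concurrent recruitment) | Mean gap | Trials with a gap of 6 or more in some centre |
|---|---|---|
| Centre × sex × age, blocks of 10, four cells per centre | 3.0 | 34% |
| Same, six cells per centre | 3.9 | 67% |
| Centre × sex, blocks of 6 | 1.4 | 0% |
| Centre × sex, blocks varying among 3, 6 and 9 | 1.5 | 0.1% |

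Adding centre while keeping age strata and blocks of ten therefore solves only part of the problem.

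**The case against.** The strongest reply is that little is at risk for inference. Individual randomisation is unbiased whether or not centre is a stratum, chance differences between sites are part of the sampling error, and a centre term in the model would recover most of what is lost, at a precision cost of only 3–5%. All of that stands. An analysis plan or the full protocol, not shown here, may also contain such a term. The point therefore rests on the strata and block size that the article states, not on the silence about centre in the analysis.

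The trial-level percentages describe the worst of five centres. A single centre under sequential recruitment reaches a gap of 6 in fewer than one case in five. Staggered opening also reduces the imbalance, because successive centres use consecutive parts of the same lists, so the concurrent figures are an upper bound. Staggering matters because it links centre to season, and even that link is coarse: three openings fall in January or February and two in September or November.

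A reader might go further and infer that many SENWI groups will be too small to function. The article sets no minimum group size, and control patients, who count in the any-arm figure, have no group sessions. Nor does it say how the two session times divide the groups; they may be a choice of slot. A reader might also infer that centre fixes the instructor, but no section assigns instructors by centre, and all follow a standardised protocol. That centre strongly predicts attendance or activity is plausible, but no figure in the article shows it.

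The remedy has a cost too. With small blocks of fixed size within a centre, staff who know earlier allocations in an open-label trial could sometimes deduce the next one. This matters because nurses enrol, and the section on medication intake also gives them a part in randomisation.

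**Conclusion.** The point holds as an avoidable weakness of design, not as a source of bias. The stated rule leaves the split of arms within each centre to chance and uses a block size that does not fit three arms, while centre is tied to place and season. The typical gap of about 4 on about 29 people is modest. A gap of 6 or more somewhere in the trial is more likely than not: about 60% if centres recruit in sequence and up to about 86% if they recruit together. The percentages depend on the assumed centre sizes, number of age bands and overlap of recruitment; other assumptions tried gave 50–87%.

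The documents do not support the stronger reading that arm contrasts will be biased, that most centres will be badly uneven, or that SENWI groups will usually be too small. The consequences are chance imbalance by site and season, uneven walking groups and a small loss of precision. The change is worth making because it is cheap and four of the five centres had yet to open at submission.

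**What to change.** For everyone not yet randomised (144 − 40 = 104 people at submission, if all 40 enrolled had been allocated):

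- Stratify by centre and sex, in place of sex and age.
- Use block sizes that are multiples of three and vary at random, for example 3, 6 and 9. Hold the lists centrally and do not disclose the sizes to recruiting staff.
- Keep age as a model covariate. It is already on the list of planned covariables.
- Include centre as a fixed effect in the mixed model and in the drop-out regression, including for those already randomised under the present rule.

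Gaps of 6 or more then occur in about 0% of trials, and the mean gap falls to about 1.5. The work is a new set of lists and one extra term per model. There are two downsides. Age balance is no longer forced by design. Smaller blocks within a centre also make allocation somewhat more predictable in an open-label trial, which varied, concealed block sizes limit but do not remove. If recruitment is complete, only the centre term can still be adopted.

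### Blocks of ten cannot be split equally over three arms, so the randomisation rule as written does not secure the planned equal allocation

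*Protocol article*

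**What the plan says.** Under Randomization and blinding, the protocol article uses a computer generator to "randomize eligible participants at the level of the individual participant", and the list is "stratified by sex and age, in blocks of ten". Under Participants, the 144 are "randomized in two intervention groups and one control group", which makes three arms. Under Sample size, the number was found "with a balanced one-way analysis of variance power calculation of 80" per cent, and the conclusion is that "48 participants will be needed in each group".

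The article gives no unequal allocation ratio. It does not give the make-up of a block of ten, the rule for the place left over after three per arm, or the number of age bands.

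**The concern.** A permuted block holds the arms at their intended ratio each time a block is filled. That works only if the block size is a multiple of the sum of the ratio. For 1:1:1 the sum is three, and ten is not a multiple of three. Either every full block is uneven, or the list was not blocked as described.

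This is more than a detail left to a fuller document. The article does state a block size, and the size it states does not fit its own three equal arms. What is at stake is whether the allocation ratio is defined at all, and whether the equal arms assumed by the balanced power calculation are secured by the procedure or left to an unstated rule. Some participants had already been enrolled when the article was submitted, so it also matters which rule they were allocated under.

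**Working it through.** **Inputs.** Block size 10, strata sex and age (Randomization and blinding). Three arms, N = 144 (Participants). 48 per arm, balanced design (Sample size). Assumed, because not stated: the rule for the tenth place, and the number of strata. I used one stratum, and four equally likely strata (two sexes by two age bands).

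**The plan's own figure.** 144 / 3 = 48, so 48 per arm means 1:1:1. Whether 48 follows from the stated power inputs is a separate question; here it is taken as given.

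**Divisibility.** 10 = 3 × 3 + 1. A full block holds three places per arm and one over, so the closest split is 4:3:3.

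**Effect on arm totals, by rule for the tenth place.**

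- *Always the same arm.* Expected totals: 144 × 0.4 = 57.6 and 144 × 0.3 = 43.2 twice, or about 58:43:43. With a single list, 14 full blocks already give that arm 14 × 4 = 56.
- *Rotated over the arms.* Three successive blocks give 4:3:3, 3:4:3 and 3:3:4, which sum to 10:10:10, so the long-run ratio is 1:1:1.
- *Drawn at random per block.* Each arm has the same expectation, 48, with more scatter than under rotation.

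**Simulation of 144 participants** (3,000 runs per setting, repeated with 6,000 runs and another seed, with agreement to within about one percentage point). Spread is the largest arm minus the smallest.

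| Block size and rule | Strata | Mean per arm | Median spread | 95th percentile | Exactly 48/48/48 |
|---|---|---|---|---|---|
| 10, same arm | 1 | 57.6 / 43.2 / 43.2 | 15 | 17 | 0 runs |
| 10, same arm | 4 | 57.6 / 43.2 / 43.2 | 15 | 19 | 0 runs |
| 10, rotated | 1 | 48 each | 2 | 3 | 26% |
| 10, rotated | 4 | 48 each | 3 | 6 | 9% |
| 10, random | 1 | 48 each | 4 | 8 | 5% |
| 10, random | 4 | 48 each | 4 | 9 | 4% |
| 6, 9 or 12 | 1 | 48 each | 0 | 0 | 100% |
| 6, 9 or 12 | 4 | 48 each | 2 | 4 to 6 | 10 to 18% |

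**What the worst case would cost.** The variance of a difference between two arm means is proportional to 1/n₁ + 1/n₂. Relative to 48 against 48:

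- two smaller arms: (2/43.2) / (2/48) = 1.11
- larger against smaller arm: (1/57.6 + 1/43.2) / (2/48) = 0.97

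Omnibus one-way ANOVA power at the 5% level with N = 144, under assumed differences in SD units:

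| Arms | One arm differs by 0.5 SD | Means 0, 0.25, 0.5 SD |
|---|---|---|
| 48:48:48 | 0.71 | 0.57 |
| 58:43:43 | 0.74 if the large arm differs, 0.68 if a small one does | 0.53 at worst |
| 50:48:46 | within about 0.01 of 0.71 | within about 0.01 of 0.57 |

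**The case against.** The strongest reply is that little harm follows. ANOVA and mixed models do not need equal arms, a 4:3:3 block introduces no bias, and if the tenth place rotates or is randomised the arms differ by only a few participants. The article may have left the within-block rule to a fuller protocol, or ten may be a reporting slip. The remedy also has limits: with four assumed strata, blocks that are multiples of three give exactly 48 per arm in only 10 to 18% of runs, because the last block in each stratum is usually incomplete. All of this stands as a limit on severity. It does not remove the conflict, because ten and three equal arms do not fit together whatever a fuller document adds, and the article gives no rule that would reconcile them.

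A reader might infer more than the document supports:

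- *That 48 per arm cannot be reached.* This does not follow. Under rotation or random assignment the arms average 48 and sometimes land on it exactly. The 58:43:43 split needs a rule that the article does not state.
- *That 144 not being a multiple of ten is itself a fault.* Incomplete last blocks occur in any stratified blocked list.
- *That centre must be a stratum, or that walking groups may be too small.* The article promises no balance by centre and gives no minimum group size. Leaving centre out is a legitimate choice, and the group-size worry is conjecture.
- *That a fixed, published block size makes allocation predictable.* The article says that a research member randomises, that nurses enrol, and that the list is withheld until baseline is complete, which largely answers this. Very small blocks would be easier to guess, not harder. Other sections word the nurses' part in allocation differently, but that concerns who allocates, not the block size.

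**Conclusion.** The point holds in a limited form. A block of ten cannot be balanced over three arms, so the published rule conflicts with the 1:1:1 design and does not secure the equal arms assumed in the power calculation. That much is arithmetic and needs no assumption.

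The consequence cannot be fixed from the document, because it depends on the unstated rule for the tenth place. The assumed worst case is about 58:43:43, which lowers power by roughly 0.03 to 0.04 in the least favourable configurations examined. Under the two more ordinary rules the median gap between the largest and smallest arm is 2 to 4 participants, and power hardly moves. The simulated figures rest on assumed strata of equal expected size. The defect lies in how the allocation is specified. It gives no ground for calling the comparison biased or the planned arm size unreachable.

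**What to change.** For participants not yet randomised, replace the block size of ten with a multiple of three (for example 6, 9 or 12, or a random mix of these) within the existing sex and age strata, and state the 1:1:1 ratio. Every complete block then splits 2:2:2, 3:3:3 or 4:4:4.

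For the 40 volunteers reported as enrolled under Trial status, report the list, block composition and ratio actually used for those already randomised, including how the tenth place was assigned. If ten was a reporting slip, a correction giving the true size is enough.

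The cost is a newly generated list and a short amendment. By the article's own schedule four of the five centres had not begun recruiting at submission, and 144 − 40 = 104 participants were still to be enrolled, so most of the trial could run under the corrected rule. The sample size and the analysis model need not change. Exact equality at 144 should not be promised, because incomplete blocks within strata will still leave small differences.
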